### Feasibility Criteria for Progression to Full Trial

The primary objective is to evaluate the feasibility and acceptability of the intervention, its implementation, and the trial procedures for the subsequent cRCT. We must establish indicators on what procedures to carry on to the full trial and where modifications should be made to study design or content. The overall feasibility and acceptability will be determined in the intervention arm by the following criteria at the end of the study to determine progression to the full trial:

- Identification of qualitative themes reporting that both PCWs and clients perceive group primary care mental health services as being acceptable, feasible, and appropriate
- Retention of at least 67% (27/40) of PCWs and patients through end line assessments
- Fewer than 15% (15/98) of missing items on outcome measures across all assessments or fewer than 15% (eg, 3/22 items on the R-DAQ) for each questionnaire with more than 10 items) or 50% (eg, 4/9 items on the PHQ-9; for each measure with 10 items or fewer) of missing items on an individual assessment.
- Presence of adverse events among fewer than 10% (4/40) of the participants and any serious adverse events.

In domains where criteria are met, we will retain the procedure for the full trial. In domains where criteria are not met, we will modify the procedures for the full trial, guided by data collected during interviews. The presence of any adverse events and/or serious adverse events will be addressed by the trial team to identify alternative strategies for the full trial and data safety monitoring committee. The number of feasibility and acceptability criteria that are not met will determine the extent of intervention and trial design modification. Ethical approval for this feasibility study was obtained from the following collaborating institutions:

- Psychiatry, Nursing, and Midwifery Research Ethics Committee, King's College London, United Kingdom (May 2020)
- University of Ibadan and University College Hospital Joint Ethics Committee, University of Ibadan, Nigeria (December 2018)
- Nepal Health Research Council for the Transcultural Psychosocial Organization Nepal (October 2020)
- WHO Ethics Review Committee, WHO, Geneva (May 2020).

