### Aims and Objectives

Emilia aims to test the feasibility of an updated electronic Mental Health Gap Action Programme Intervention Guide (e-mhGAP-IG) and trial procedures for the future conduct of a large-scale trial, which would evaluate differences in depression detection between facilities using the e-mhGAP-IG versus the paper mhGAP-IG. The objectives of this feasibility study, in preparation for a future trial, include the following:

1. To evaluate the feasibility and overall implementability of primary care mental health services using the e-mhGAP-IG for training, supervision, and delivery of care (primary objective).
2. To determine recruitment and retention rates of PCWs and patients.
3. To establish the acceptability and feasibility of assessing PCW and patient outcomes.
4. To assess ethics and safety procedures using adverse event reporting.
5. To describe depression detection rates in primary health clinics (PHCs).
6. To describe depression treatment outcomes in PHCs.

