#### Patient Data

We estimate screening a minimum of 400 patients at each site during the pretraining enrollment period and 1200 patients in the posttraining enrollment period (starting 3 months after the mhGAP-IG training). In the posttraining period, we will include a subset of patients who have received a health worker depression diagnosis to follow-up for treatment outcomes. We will follow up with them at approximately 3 months after they are screened to measure their treatment outcomes. A subset of patients will also participate in FGDs to assess their perspectives on the acceptability (AIM) and appropriateness (IAM) of the intervention 3 months after their baseline health care appointment.

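### The progression criteria are meant to cover the procedures of a two-arm trial but are judged in the intervention arm only, and the acceptability criterion names a group service that neither arm delivers

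*Protocol*

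**What the plan says.** The Protocol section Feasibility Criteria for Progression to Full Trial sets the objective as being to "evaluate the feasibility and acceptability of the intervention, its implementation, and the trial procedures for the subsequent cRCT". It then fixes where this is judged: "The overall feasibility and acceptability will be determined in the intervention arm by the following criteria at the end of the study". Four criteria follow:

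- a criterion on views of the service, which looks for qualitative themes showing that "both PCWs and clients perceive group primary care mental health services as being acceptable, feasible, and appropriate";
- a minimum for follow-up, which is worded as "Retention of at least 67% (27/40) of PCWs and patients through end line assessments";
- a limit on incomplete questionnaires, given first as "Fewer than 15% (15/98) of missing items on outcome measures across all assessments", with alternative limits for single questionnaires;
- a safety limit, which is worded as "Presence of adverse events among fewer than 10% (4/40) of the participants and any serious adverse events".

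Where a criterion is met, the procedure is kept for the full trial. Where it is not met, the procedure is modified. No stop outcome is stated.

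Aims and Objectives describes the future trial as a comparison of facilities using the electronic guide with facilities using the paper guide. One objective is "To determine recruitment and retention rates of PCWs and patients", and others concern the assessment of outcomes and the safety procedures. None of these is limited to one arm. Patient Data, under Implementation Data, has a subset of patients join focus groups to "assess their perspectives on the acceptability (AIM) and appropriateness (IAM) of the intervention 3 months after their baseline health care appointment".

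**The concern.** The stated scope and the stated arm do not fit together. Acceptability of the e-mhGAP-IG can only be judged where it is used. Retention, completeness of questionnaires and adverse event reporting are different: they are features of running the trial, and a comparison of electronic with paper guides depends on them in both arms. A feasibility trial with a control arm is the place to learn whether control clinics can be kept in the study and measured. The rule as written leaves that evidence out of the decision it is meant to inform.

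The first criterion has a separate fault. It asks for views on a kind of service that the trial does not deliver, and it asks clients about a property that their focus groups are not planned to cover. This fault does not cause the control-arm gap, but it sits in the same list and needs correcting with it.

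**Working it through.** **1. Reproduce the printed threshold.** 0.67 × 40 = 26.8, so 27 must be retained. 27/40 = 67.5% passes and 26/40 = 65.0% fails. The printed 27/40 is arithmetically right.

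**2. Compare the denominator with the plan.** The Abstract (Methods) gives 20 health workers per arm in Nepal and 15 per arm in Nigeria. The intervention arm is therefore 20 + 15 = 35, and both arms together are 70. Among health workers, 40 is the Nepal total over both arms (Participants; Statistical Power and Sample Size Calculation). It is not an intervention-arm number. For 35, 0.67 × 35 = 23.45, so 24 must be retained (24/35 = 68.6%).

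**3. Count who is outside the rule.** Health workers: 70 − 35 = 35, or 50%. Patients: Participants expects about 200 screened per arm per country per month. In the control arm that is 200 × 1 month × 2 countries = 400 before training and 200 × 3 months × 2 countries = 1,200 after it. The number to be followed up is not given, so no patient retention count is worked out here.

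**4. Apply the rule.** With 24/35 retained in the intervention arm, the health worker part of the retention criterion is met whatever happens in the control arm, including 0/35.

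The following illustration uses assumed retention rates that are not in the Protocol. It treats health workers as independent, with X binomial on 35 and a pass at X ≥ 24.

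| Assumed true retention | Chance of reaching 24/35 |
|---|---|
| Intervention 85% | 0.996 |
| Control 50% | 0.020 |
| Control 60% | 0.195 |

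The rule as written passes with probability 0.996 in either scenario. If both arms had to reach 24/35, the probability would be 0.996 × 0.020 = 0.020 with control at 50%, or 0.996 × 0.195 = 0.194 with control at 60%.

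**5. Set the acceptability criterion beside the intervention.**

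- Intervention Condition, Control Condition and Table 1 list a guide, remote supervision and training. None lists a group service for patients.
- The Technology section describes a patient mode for a visit with one individual.
- In Remote Supervision, group is a possible format for supervising health workers. Elsewhere in data collection it refers to focus groups.
- The criterion requires clients to judge feasibility. The planned patient focus groups name acceptability and appropriateness.

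**6. Two other printed examples.** 4/40 = 10.0%, which is not fewer than 10%. 15/98 = 15.3%, which is not fewer than 15%. These are side points, but the examples will have to be redone once the denominators are corrected.

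**The case against.** The strongest reply is that control-arm evidence is not lost. The objectives on recruitment, retention, outcome assessment and safety carry no arm limit. Study Design says the data will be used to refine the intervention, with randomization and recruitment among its examples. The progression section also says that any adverse event will be addressed by the trial team, with no arm limit in that sentence. Poor control-arm retention would be seen and could be acted on. All of this stands. What is missing is a control-arm criterion in the formal rule.

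Several stronger readings are tempting, but the document does not support them.

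- A reader might infer that a failed control arm leads to progression that would otherwise be blocked. The rule is retain or modify with no stop outcome, so failure in the intervention arm does not block the full trial either. The effect of the restriction is that a failing procedure is not flagged for change.
- A reader might infer that good results in Nepal can hide poor ones in Nigeria, since 20/20 plus 4/15 (27%) makes 24/35. That assumes the countries are pooled to 35. The section does not say so and prints 40.
- A reader might expect paper-guide clinics to lose more participants. Nothing in the Protocol predicts this, and both arms receive training and remote supervision.
- A reader might conclude that the acceptability criterion can be neither met nor failed. PCWs Data and Supervisor Data, under Implementation Data, make the intended object clear: the mhGAP-IG and remote supervision for health workers, and remote supervision for supervisors. Implementation Outcome Analysis also brings patient transcripts into the overall assessment of feasibility. The fault is one of wording.

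**Conclusion.** The concern holds as a mismatch between stated scope and stated rule. Three of the four progression criteria measure trial procedures, yet the control arm (35 of 70 planned health workers, and all control patients) does not enter them. A procedure that fails in paper-guide clinics would formally be classed as met and retained. The count rests on the Protocol's own staffing estimates, whereas the probabilities rest on assumed retention rates and ignore clustering by clinic. The denominator of 40 does not describe the population to which the rule is said to apply. The group wording and the client feasibility element are separate, smaller errors in the same list. The change is worth making before the criteria are applied, but nothing here shows that the trial itself is unsound.

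**What to change.** Apply the retention, missing-item and adverse-event criteria to each arm. State them separately for health workers and patients, with denominators that match the plan (35 health workers per arm on current estimates) and with worked examples that satisfy their own limits. Report the between-arm difference in retention. Keep only the acceptability and feasibility of the e-mhGAP-IG as intervention-arm criteria. In the first criterion, replace the reference to group services with the e-mhGAP-IG and remote supervision, and limit the client part to acceptability and appropriateness.

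Report the same figures by country descriptively, without a pass/fail threshold in each country-by-arm cell. Such thresholds would be 14/20 in Nepal and 11/15 in Nigeria in each arm. At an assumed true retention of 80%, with independence, the chance of passing all four cells is (0.913 × 0.836)² = 0.58, which is too strict for groups of this size.

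The cost is rewording plus tabulation of data already planned in both arms. The criteria also become somewhat harder to meet. For health worker retention at 24/35 per arm, the chance of passing falls from 0.966 for one arm to 0.966² = 0.93 for both at an assumed 80% retention, and from 0.858 to 0.858² = 0.74 at an assumed 75%.

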#### Outcome Data

##### PCWs Data

PCWs will be interviewed by a member of the research team during a 1-week period at each PHC clinic at 4 time points: (1) before mhGAP-IG training, (2) immediately post training, (3) 3 months post training, and (4) 8 months post training. During the research interviews, all PCWs will complete quantitative assessments, assessing 5 variables related to the PCW outcomes:

1. mhGAP-IG Knowledge Scale: In the mhGAP-IG training, knowledge is assessed by a standardized set of 30 questions in the multiple-choice question format, the mhGAP-IG Knowledge Scale. These are administered before and after training to measure the change in knowledge.
2. Revised-Depression Attitude Questionnaire (R-DAQ): Previously used in both Nepal and Nigeria, the R-DAQ [\[40\]](#) assesses clinicians' views and understanding of depression. The R-DAQ 22-item scale asks clinicians to rate each item as *strongly disagree*, *disagree*, *neither disagree nor agree*, *agree*, or *strongly agree*. Examples of items include "depression is a disease like any other (eg, asthma, diabetes)," "psychological therapy tends to be

unsuccessful with people who are depressed,” and “becoming depressed is a natural part of being old.”

3. Social Distance Scale (SDS): The SDS was designed by Bogardus [41] to measure the level of acceptability of various types of social relationships between Americans and members of common ethnic groups [42,43]. The modified SDS has been widely used to measure mental health-related stigma and to understand the importance of labels attached to people with former mental illnesses [42,44]. The modified version consists of 12 items that represent social contact with different degrees of distance. The SDS measures the acceptability of different degrees of social distance and thus, by inference, the attitude of the respondent to the person with the condition [45]. The SDS sum score represents the attitude of the respondent toward the condition. The SDS has been used in global mental health research. Among stigma measures, it has been shown to be most strongly associated with health worker competence [46].

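### As printed, the missing-data progression criterion can be met by its pooled limit alone, so the per-questionnaire limits cannot fail it

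*Protocol*

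**What the plan says.** The protocol, under Feasibility Criteria for Progression to Full Trial, lists four criteria judged in the intervention arm at the end of the study. The missing-data criterion opens with a pooled limit: "Fewer than 15% (15/98) of missing items on outcome measures across all assessments". It continues with *or* ("missing items on outcome measures across all assessments or fewer than 15"%) and a 15% limit by questionnaire ("eg, 3/22 items on the R-DAQ) for each questionnaire with more than 10 items"), then a second *or* and a limit for short measures: "50% (eg, 4/9 items on the PHQ-9; for each measure with 10 items or fewer) of missing items on an individual assessment".

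The consequence of passing is given in the same section: "In domains where criteria are met, we will retain the procedure for the full trial". Where a criterion is not met, the procedure is modified, guided by interview data.

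The section does not say which measures make up the 98 items. It also does not say whether the pooled and per-questionnaire limits must both hold.

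**The concern.** The first *or* joins two levels of aggregation of the same data. Read as printed, it gives two routes to a pass. Whenever the pooled limit is met, the questionnaire limits cannot change the result; they can only rescue a criterion that the pooled limit has failed.

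A pooled average hides the failure of one scale. Such a failure is foreseeable here: Measure Translation and Adaptation says that the PSS had not yet been translated and adapted for Nigeria. Objective 3 under Aims and Objectives is to establish whether PCW and patient outcomes can acceptably and feasibly be assessed. A rule that can pass when one scale has failed, or that may leave patient measures out of its pooled route, does not test that objective well, and a faulty procedure could be carried into the full trial.

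**Working it through.** **Inputs.** All counts are from the protocol, Outcome Data.
- mhGAP-IG Knowledge Scale: 30 items ("standardized set of 30 questions in the multiple-choice question format").
- R-DAQ: 22 items ("The R-DAQ 22-item scale asks clinicians to rate each item").
- Social Distance Scale (SDS): 12 items ("The modified version consists of 12 items that represent social contact with different degrees of distance").
- PSS: 19 items.
- ENACT: 15 items, stated for the service-user version only. The clinician version's count is not given, so 15 is an assumption.
- PHQ-9: 9 items. WHODAS 2.0: 12 items.

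**Step 1: the plan's own denominator.** 30 + 22 + 12 + 19 = 83, and 98 − 83 = 15. The 98 is reproduced by the five PCW outcome scales if the ENACT clinician version has 15 items. The sum alone does not prove this: putting the 12-item WHODAS 2.0 in place of the SDS, or the service-user ENACT in place of the clinician version, also gives 98. The five PCW scales are the natural reading because the protocol lists them together.

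**Step 2: the pooled limit.** 0.15 × 98 = 14.7 items. On one set of forms, 14 missing items (14.3%) pass and 15 (15.3%) fail, so the printed 15/98 works only as an exclusive bound.

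**Step 3: one scale incomplete, all others complete.** Each scale is assumed to be given equally often. If a proportion *p* of a *k*-item scale is missing, the pooled proportion is *p* × *k*/98. It stays under 15% when *p* < 14.7/*k*.

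| Scale | k | Wholly blank, k/98 | Pooled limit | Largest *p* that passes (just under) | Own limit |
|---|---|---|---|---|---|
| SDS | 12 | 12.2% | met | no bound (100%) | 15% |
| ENACT (15 assumed) | 15 | 15.3% | failed | 98.0% | 15% |
| PSS | 19 | 19.4% | failed | 77.4% | 15% |
| R-DAQ | 22 | 22.4% | failed | 66.8% | 15% |
| Knowledge | 30 | 30.6% | failed | 49.0% | 15% |

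Only a scale of 14 items or fewer can be wholly blank and pass. Every scale can, however, be missing more than three times its own limit and pass (the smallest ratio is 49.0/15 = 3.3).

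**Step 4: sensitivity to the denominator.**
- ENACT clinician version with 10 to 20 items: the five scales total 93 to 103, and a blank SDS gives 12.9% to 11.7%. It passes throughout.
- All eight outcome scales pooled: 98 + 9 + 12 + 15 = 134 items. Wholly blank, the PHQ-9 (6.7%), SDS and WHODAS 2.0 (9.0% each), either ENACT (11.2%) and PSS (14.2%) pass; the R-DAQ (16.4%) and Knowledge Scale (22.4%) fail.
- Items pooled over persons and visits, for the intervention arm in Nepal. Assumed: 20 PCWs × 4 visits × 98 items = 7,840, plus 800 patients (200 a month for 1 + 3 months) × 36 items (9 + 12 + 15) = 28,800; total 36,640. Any one PCW scale wholly blank is 2.6% (SDS, 960/36,640) to 6.6% (Knowledge, 2,400/36,640) and passes. A wholly blank patient scale is 19.7% (PHQ-9) to 32.8% (service-user ENACT) and fails.

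Which scales escape depends on the denominator. That at least one can escape does not, on any of these variants.

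**Step 5: both limits required.** A blank SDS still meets the pooled limit at 12.2% but is 12/12 = 100% missing against its own 15%, so the criterion fails.

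**The case against.** The strongest reply is that *or* in this bullet merely lists limits that all apply. The second *or* does work that way: it sorts limits by scale length and cannot be another route to a pass. The authors may have meant the first in the same sense. That is possible, but the text does not say so, and the first *or* links a pooled limit to per-questionnaire limits, not one scale length to another. On the list reading a blank SDS fails; on the printed reading it passes. The wording should settle this before the data are seen.

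A second reply concerns the unit. The bullet ends by referring to a single assessment, so its per-questionnaire limits may describe one completed form. This stands, and it rules out a bare swap of *or* for *and*: one PCW leaving 4 of 22 R-DAQ items blank (18.2%) could then fail the whole criterion.

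Third, the section is not a single go/no-go rule. Procedures are kept or modified by domain, interviews guide changes, and retention has its own criterion. A scale blank in everyone is a limiting case whose likelihood is not estimated here. This limits the consequence but does not repair the rule.

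A reader might also infer more than the documents support:
- That any scale could be blank and pass. On 98 items, four of the five PCW scales would fail.
- That a wholly blank PHQ-9 passes at 9/98 = 9.2%. If the 98 is the five PCW scales, the PHQ-9 is not in it and that fraction does not arise. A patient-only pool of 36 items would put it at 9/36 = 25%, a failure. A wholly missing PHQ-9 would also leave no accuracy outcome and could not go unnoticed.
- That AIM and FIM belong in this criterion. The protocol places them under implementation data, and the criterion concerns outcome measures.

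**Conclusion.** The concern holds for the sentence as printed. The pooled limit alone can satisfy the missing-data criterion, and the per-questionnaire limits then have no effect. On the protocol's own denominator, a wholly blank SDS passes at 12.2%, and the R-DAQ or PSS can be missing up to about 67% or 77% when the rest is complete, each against a stated limit of 15%. Wholly blank scales of 15 or more items fail.

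The size rests on the SDS, R-DAQ and PSS being within the 98 and on scales being given equally often. It does not rest on the ENACT count, because 98 is the protocol's figure.

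That patient outcome measures may lie outside the pooled route is weaker. It rests on reading the 98 as the five PCW scales, which needs an item count that the protocol does not give, and the same bullet speaks of all assessments and uses the PHQ-9 as an example. The documents do not establish that patient missingness is ignored, only that the denominator is undefined.

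This is a fault in a stated decision rule and should be corrected. It is not a safety matter.

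**What to change.** Restate the criterion at the level of the measure, for example: *Fewer than 15% of items are missing over all listed outcome measures combined, and, for each PCW and patient outcome measure separately (including PHQ-9 and WHODAS 2.0), the proportion of its items missing over all participants and visits is below 15% if it has more than 10 items, or below 50% if it has 10 or fewer.*

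List the measures and item counts that make up the pooled denominator, including the count for the ENACT clinician version. If a limit for a single form is also wanted, give it as a separate rule for when that form counts as complete.

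The cost is this wording and a short list; the data are already to be collected. The downside is a stricter criterion that can fail on one measure. Because the section modifies procedures by domain, such a failure would call for changing how that measure is collected and need not stop progression.

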On the basis of prior data on primary care service use and screening depression rates, we anticipate being able to screen approximately 50% of adult patients presenting to primary care, with a possibility of screening a higher percentage depending on patient flow in the facility [33]. Therefore, we anticipate screening approximately 200 patients per arm per country per month (ie, 400 patients per country in the 1-month pretraining patient enrollment period and 1200 patients per country in the 3-month posttraining patient enrollment period).

Inclusion criteria for patients to be screened include the following:

- Attending PHC for treatment of a new case at recruitment
- Reached the age of adulthood (ie,  $\geq 18$  years)
- Fluent in Nepali (Nepal only) or English or Yoruba (Nigeria only).

Adult attendees will be deemed ineligible for the study if they are unable to understand or complete study assessment (eg, individuals with severe learning disability or dementia), unable to provide informed consent, or have a medical emergency requiring immediate intervention.

All patients who meet the eligibility criteria and choose to enroll in the study will then be screened by a research assistant to determine their depression status. Following this screening, patients will be evaluated by a PCW who will make an independent diagnosis without speaking to the research assistant or reviewing the screening results. Administration of screening tools may occur before or after the patient meets the health worker based on the workflow of the clinics. After patients meet the PCWs, a research assistant will review the provider's case notes to document whether or not a depression diagnosis was made.

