5. Suicidal ideation and behavior: Suicidal ideation and behavior will be assessed, in Nepal only, using suicidality questions adapted from the Composite International Diagnostic Interview suicidality module [57]. This tool has been widely used in Nepal [58]. We will ask participants whether they had thought of taking their own life in the past 12 months. Those who will respond affirmatively to the ideation question will be asked if they had made a plan to take their own life. In Nepal, those who meet the criteria for current suicidal thoughts or those who attempted suicide in the past 3 months will be immediately referred to a trained psychosocial counselor. In Nigeria, patients endorsing the suicidal ideation item from the PHQ-9 will receive further assessment of suicide risk in line with local protocols.

Confirmation of diagnosis and treatment initiation will be collected from the clinical notes by PCWs. Patients interviewed in the first 3 months of data collection and who screen positive for depression will be invited to participate in a follow-up interview 3 months after their first appointment. The interview will consist of quantitative assessments of depression (PHQ-9), disability (WHODAS 2.0), therapeutic alliance (the ENACT-service user version), and suicide ideation and action Composite International Diagnostic Interview. Treatment details will be extracted by the research team from patient records to document treatment retention.

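### As worded, the adverse-event and retention progression criteria use denominators that do not match the people followed, and the printed 40 fits no stated intervention-arm group

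*Protocol*

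**What the plan says.** Protocol, Feasibility Criteria for Progression to Full Trial, sets the arm: "The overall feasibility and acceptability will be determined in the intervention arm by the following criteria". Two of the criteria are "Retention of at least 67% (27/40) of PCWs and patients through end line assessments" and "Presence of adverse events among fewer than 10% (4/40) of the participants". The section does not say who makes up the 40, or whether PCWs and patients are counted together.

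On who is enrolled, the Participants section says "All patients who meet the eligibility criteria and choose to enroll in the study will then be screened by a research assistant". Enrolment therefore comes before the PHQ-9 result. On volume, the same section says "we anticipate screening approximately 200 patients per arm per country per month", for one month before training and three months after.

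On who is seen again, there are two descriptions. Patient Data under Implementation Data follows a subset of post-training patients who received a health worker diagnosis of depression. Patient Data under Outcome Data instead takes patients from the first three months of data collection "who screen positive for depression will be invited to participate in a follow-up interview 3 months after their first appointment". Neither describes a second study assessment for screen-negative patients, or for patients enrolled before training.

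**The concern.** A proportion used as a decision limit should be taken over people in whom the event can be seen. Here most enrolled patients have one planned contact. If they count in the adverse-event denominator, they add to the bottom of the fraction and little or nothing to the top, so the criterion can be met while events are common among patients under observation. If they count in the retention denominator, the opposite happens: people never due a second visit are scored as lost.

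The number of unmet criteria decides how far the intervention and trial design are modified, and Aims and Objectives lists both retention of PCWs and patients and the assessment of safety procedures. A rule whose result turns on an unstated denominator does not serve those aims.

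**Working it through.** **1. The plan's own counts.** 27/40 = 67.5%, and 26/40 = 65%, so 27 is the smallest count of 40 that meets 67%. 4/40 = 10.0% exactly, so it does not satisfy fewer than 10%; 3/40 = 7.5% does.

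**2. Does 40 fit a group in the intervention arm?**

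- PCWs per arm (Abstract, Methods): 20 in Nepal and 15 in Nigeria, 35 together.
- 40 is Nepal's PCW total over both arms (Participants; Statistical Power and Sample Size Calculation).
- 40 is also the minimum number of screen-positive patients needed, in the pre-training month and the first post-training enrolment month, to run the within-arm detection comparison (Statistical Power and Sample Size Calculation). That is not a follow-up cohort, and no follow-up is planned for pre-training patients.

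So no stated intervention-arm group has 40 members.

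**3. Enrolled patients per arm per country.** 200 × 1 month + 200 × 3 months = 200 + 600 = 800. Over both arms this reproduces the plan's 400 pre-training and 1200 post-training patients per country.

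**4. Patients eligible for the 3-month interview.** The protocol gives no screen-positive rate, so I take a range. The lower value is the quoted depression rate (Settings: 16.8% Nepal, 5.5% Nigeria). The upper value applies the PHQ-9 accuracy figures (Patient Data under Outcome Data: sensitivity 94% and 85%, specificity 80% and 99%):

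rate = prevalence × sensitivity + (1 − prevalence) × (1 − specificity)

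- Nepal: 0.168 × 0.94 + 0.832 × 0.20 = 0.324
- Nigeria: 0.055 × 0.85 + 0.945 × 0.01 = 0.056

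Multiplying by the 600 post-training patients:

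| | Nepal | Nigeria |
|---|---|---|
| Eligible for follow-up | 101 to 195 | 33 to 34 |
| As share of 800 | 12.6 to 24.3% | 4.1 to 4.2% |

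If only diagnosed patients are followed, the protocol's example detection rate of 53% gives 53 to 103 in Nepal and about 18 in Nigeria, counting diagnosed patients who also screen positive.

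**5. Adverse-event criterion over all enrolled patients.** Suppose 30% of followed patients have an event and none is recorded in anyone else. The displayed proportion is 0.30 × followed / 800:

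- Nepal: 0.30 × 100.8/800 = 3.8%, up to 0.30 × 194.6/800 = 7.3%
- Nigeria: 0.30 × 33/800 = 1.2%, up to 0.30 × 33.7/800 = 1.3%

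All are below 10%. The limit is 0.10 × 800 = 80 people, which is 41 to 79% of the Nepal follow-up group (80/194.6 to 80/100.8) and more than the whole Nigeria group. Adding PCWs with the same 30% rate does not change this at the upper rates: 0.30 × (194.6 + 20)/820 = 7.9% and 0.30 × (33.7 + 15)/815 = 1.8%.

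**6. Retention criterion.** Over all enrolled patients, the ceiling with perfect follow-up is the share in step 4: about 13 to 24% in Nepal and 4% in Nigeria. Pooling PCWs lifts the upper values only to (195 + 20)/820 = 26% and (34 + 15)/815 = 6%. Over people who are due an end line assessment, 67% is attainable: with 40 such people and true retention of 75%, the binomial chance of keeping at least 27 is 0.90.

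**The case against.** The strongest reply is that the section prints its own base. On 40 people nothing is diluted and 67% is reachable, so the figures on 800 test a denominator that the authors did not write. This stands in part: 27/40 and 4/40 are clearly not on a base of 800. But step 2 shows that the 40 cannot be matched to a group in the arm where the rule is applied, and if it means PCWs, the safety criterion leaves patients out altogether.

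A reader might infer that 67% patient retention cannot be reached. The documents do not support that. The phrase "of PCWs and patients through end line assessments" can fairly be read as covering only people due such an assessment, and a screen-negative patient cannot be lost from a visit never scheduled. The adverse-event criterion has no such limiting phrase, so the concern is stronger there.

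A reader might also infer that events in once-seen patients go unobserved. That is not shown either. Adverse event reporting is named as a procedure without being tied to the 3-month interview, and patients are interviewed at their first contact. What can be said is that these patients have no planned follow-up contact.

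Finally, the consequence should not be overstated. Unmet criteria lead to modified procedures rather than a stop, and the trial team is to address any adverse event whatever the percentage. That limits the harm, but the 10% and 67% limits still need a defined base.

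**Conclusion.** The concern holds as a defect in the wording of two decision limits. Either the adverse-event proportion is taken over all enrolled participants, where 30% among followed patients shows as about 4 to 7% in Nepal and about 1% in Nigeria and passes, or it rests on a count of 40 that fits no stated intervention-arm group. For retention, the ceilings of about 13 to 24% and 4% apply only on the literal all-enrolled reading.

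These sizes assume that screening targets are met, that screen-positive rates lie at 16.8 to 32.4% in Nepal and 5.5 to 5.6% in Nigeria (the Nigerian prevalence is not stated to be a clinic figure), that everyone eligible takes up follow-up, and that counted events arise among followed patients. The 30% is an illustration and does not come from the protocol.

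**What to change.** In Feasibility Criteria for Progression to Full Trial:

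- Apply the 67% and 10% limits separately to (a) intervention-arm PCWs enrolled at baseline and (b) intervention-arm patients eligible for the 3-month interview.
- Report events in once-seen patients alongside as counts, still reviewed by the trial team.
- Replace 27/40 and 4/40 with counts that fit those groups. For PCWs by country, 67% means at least 14 of 20 (0.67 × 20 = 13.4) and 11 of 15 (0.67 × 15 = 10.05), and fewer than 10% means at most 1 of 20 or 1 of 15. Patient counts follow once the cohort is settled.
- Reconcile the two Patient Data sections on whether diagnosed or screen-positive patients are followed, since that defines group (b).

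The cost is a wording change with no new data. The adverse-event proportion may look less favourable, and the separate denominators are small, so one or two PCWs can decide a criterion.
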